**Additional File 2 - Neuroimaging Substudy Analysis Plan**

**Optimal Timing of Anticoagulation After Stroke: A Randomised Controlled Trial: Neuroimaging-based Secondary Analysis Plan**

[name]^1^, [name]^1^, [name]^2^, [name]^3^ and [name]^1^

1. Stroke Research Centre, Department of Brain Repair and Rehabilitation, UCL Queen Square Institute of Neurology, London, UK.
2. UCL Queen Square Institute of Neurology, University College London, London, UK.
3. Department of Neuroradiology, National Hospital for Neurology and Neurosurgery, University College London Hospitals NHS Trust, London, UK.

*Introduction and rationale*

When to start anticoagulation after acute ischaemic stroke in patients with AF is a frequent and important dilemma in stroke medicine. Several randomised trials have been undertaken with the aim of answering this question, including OPTIMAS, ELAN, TIMING and START (6-8, 40). However, determining the optimal timing of anticoagulation initiation for an individual patient will continue to require an individualised assessment of their risks of early recurrence and of ICH. The volume of infarcted tissue, on theoretical grounds and based on observational data (9), is an important determinant of the risk of haemorrhagic transformation. Clinical decision rules using a clinical assessment of stroke severity as a proxy for infarct size have been proposed (10,11), and stroke severity has been shown to influence anticoagulation timing in clinical practice (12). However, this approach is based only on observational data and expert opinion, and clinical stroke severity may underestimate infarct size (for example, in PCA occlusion) or overestimate it (for example, in brainstem infarction). There are also very few data on whether anticoagulation timing should be influenced by the presence of haemorrhagic transformation, or by imaging markers of cerebral small vessel disease, the major cause of spontaneous ICH and an important risk factor for symptomatic ICH following intravenous thrombolysis (13).

There is therefore a need for imaging-based analyses of data from randomised controlled trials. OPTIMAS is the largest ongoing trial in this area, with an original recruitment target of nearly 3,500 participants. Although OPTIMAS does not use imaging data to determine participant eligibility or anticoagulation timing, or obtain study-specific imaging, brain imaging performed for clinical reasons is collected for all participants, providing the opportunity for imaging-based secondary analyses. Here, we present the protocol for a neuroimaging-based sub-study in OPTIMAS, investigating the influence of infarct size and cerebral small vessel disease on the net benefit of early versus delayed anticoagulation with a DOAC after AF-associated acute ischaemic stroke.

The primary hypothesis to be tested by this sub-study is that infarct volume, assessed by MRI or CT, may modify the treatment effect of early anticoagulation with a DOAC after AF-associated ischaemic stroke, with respect to a primary outcome of all-cause stroke and systemic arterial embolism within 90 days of randomisation. We hypothesise that the treatment effect of early anticoagulation will be less favourable in patients with larger infarcts, due to higher rates of symptomatic haemorrhagic transformation. We will also test the hypothesis that a less favourable treatment effect will be seen in patients with haemorrhagic transformation of the initial infarct, and perform exploratory analyses including CT and MRI markers of cerebral small vessel disease.

methods and design

*Study setting*

The present study is a neuroimaging-based secondary analysis of OPTIMAS, a phase IV multicentre randomised controlled trial with an open-label intervention, blinded end-point adjudication, and hierarchical non-inferiority/superiority gatekeeper design, comparing a policy of early DOAC initiation, within 4 days of stroke onset, to delayed initiation, 7 to 14 days from onset, in patients with AF and acute ischaemic stroke. The primary outcome of OPTIMAS is a composite of recurrent ischaemic stroke, symptomatic ICH (including haemorrhagic transformation), unclassifiable stroke syndromes, and systemic arterial embolism incidence at 90 days post-randomisation. The target study sample size is 3,478 participants. OPTIMAS opened to recruitment in June 2019 and closed at the end of January 2024. It has recruited 3,648 participants from 100 stroke units in the United Kingdom.

*Patient population*

For each imaging exposure of interest, we will include all participants in OPTIMAS for whom the relevant imaging exposure can be assessed on imaging acquired prior to DOAC administration. We will exclude participants for whom the imaging exposure of interest cannot be measured due to absence of the relevant imaging modality or the failure to acquire images of diagnostic quality (as assessed by the OPTIMAS imaging rating team). For measurement of infarct size when participants have both MR and CT available to assess, we will segment the infarct in MRI owing its higher diagnostic accuracy, and when more than one CT is available we will choose the latest one prior to commencement of DOAC.

When stroke onset is unknown and cannot be estimated clinically with reasonable confidence, it should be determined in accordance with the main study protocol i.e. taken as the time the patient was last known to be well.

*Imaging data collection*

Any brain imaging performed for clinical reasons while a participant is enrolled in OPTIMAS is collected by the central study team, as well as imaging related to the qualifying stroke performed prior to randomisation. Sites send imaging via a secure online file transfer portal hosted at upload.optimas.org.uk, or exceptionally via posted CD if unable to use the online portal due to local technical or information governance requirements. Sites are required to pseudonymise imaging with the participant’s study ID prior to transfer. Files are sent in DICOM format. Once received, imaging is checked, backed up to the study imaging repository hosted by the UCL Research Data Storage service, and added to the study DICOM database (accessed via RadiAnt). Before infarct segmentation we will convert all the data to nifti format using the niftiReg software.

*Imaging data quality assurance*

The completeness of imaging data is monitored by the central study team. Sites report imaging performed to the central study team at discharge from the recruiting hospital site, and at the 90-day follow-up visit. These reports are regularly cross-checked against the imaging received, and sites contacted with prompts as needed.

On receipt, scans are checked for completeness by trained research fellows, and sites requested to resend incomplete imaging if needed. Scan quality will be assessed prior to analysis, and scans which are not of diagnostic quality excluded. When multiple eligible scans of the same modality and adequate technical quality are available, the last scan prior to DOAC administration will be preferred.

*Imaging rating procedures*

Imaging variables of interest will be rated by trained research fellows, using validated rating scales and consensus definitions when available (e.g. STRIVE, MARS) (14,15). To minimise inter-rater variability, before analysing study images, all raters will be required to rate a training set of thirty images of each modality for the primary exposures of interest and obtain an inter-rater reliability of >0.8 with the reference labels. The training set will be labelled by consultant neuroradiologists. To allow assessment of inter-rater reliability in the main study dataset, a random 10% of study images will be rated by at least two raters. Inter-rater reliability will be assessed using Krippendorff’s alpha for nominal or ordinal data, and the intraclass correlation coefficient for continuous variables. When manually segmenting CT infarcts, raters will use standard stroke windows (window 40, width 40) to identify the lesion, and these can be adjusted manually to optimally delineate the margins. If available we will segment the infarct on the thick axial slices, but we will use the thin slices if necessary for difficult cases. We will use ITKSnap version 3.6.0 to segment the infarcts.

*Automated segmentation of MR infarcts*

For the quantitative assessment of infarcts on MRI, we will utilise a deep learning segmentation model developed, validated out of sample, and described in detail elsewhere (16). In brief, this model uses the Swin UNet TRansformer (SwinUNETR) architecture with a custom loss function that optimises quantifying the volume and number of infarcts. This provides fidelity in delineating not only single infarcts but multifocal embolic ischaemia. It was trained on neuroimaging data from 10,463 patients, which includes 3563 infarct-positive diffusion-weighted imaging (B1000) cases acquired as part of routine clinical care at a tertiary neuroscience centre, and 6900 healthy controls. The model yields state-of-the-art performance evaluated on a large clinical held-out test set, with equitable performance (17) across patient demographics and all vascular territories. All model-derived lesion masks shall be reviewed and – if required – corrected by a trained reader under the supervision of an experienced neuroradiologist specialising in stroke imaging with more than 15 years of experience.

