To reflect how imaging might be used in clinical practice to decide between early and more delayed anticoagulation, we include only participants with imaging acquired before commencement of anticoagulation. We exclude imaging acquired after DOAC initiation, as this could affect some imaging features, notably the presence of haemorrhagic transformation and cerebral microbleeds. We will also consider excluding CT scans acquired fewer than 6 hours from stroke onset, as the growth of the ischaemic core and the associated development of cytotoxic oedema and CT hypodensity occurs over hours (33). We do not have an early limit on the timing of MRI, as changes on diffusion-weighted MRI appear within minutes of stroke symptom onset (34,35), although a relatively limited increase in lesion size may occur over the first 72 hours (36).

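### Infarct and haemorrhagic transformation exposures are read from the last scan before DOAC start, which is the randomised contrast, so they can be post-randomisation with an arm-dependent window

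*SAP*

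**What the plan says.** Under Patient population, the SAP includes for each exposure all participants "for whom the relevant imaging exposure can be assessed on imaging acquired prior to DOAC administration". For infarct size it prefers MRI, and "when more than one CT is available we will choose the latest one prior to commencement of DOAC". Imaging data quality assurance repeats the rule for scans of one modality: "the last scan prior to DOAC administration will be preferred". Imaging variables of interest applies it again to infarct volume and to the semiquantitative infarct size classes. The Discussion confirms that "we include only participants with imaging acquired before commencement of anticoagulation".

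Under Study setting, the trial is described as "comparing a policy of early DOAC initiation, within 4 days of stroke onset, to delayed initiation, 7 to 14 days from onset". The primary outcome counts stroke, symptomatic intracranial haemorrhage (including HT) and systemic embolism over 90 days from randomisation.

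Under Imaging data collection, "Any brain imaging performed for clinical reasons while a participant is enrolled in OPTIMAS is collected by the central study team", along with scans of the qualifying stroke made before randomisation. The trial does not obtain imaging of its own, so the timing of scans follows clinical need.

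No section limits the exposure to pre-randomisation scans, sets a time limit common to both arms, or rules out a scan made at or after an outcome event.

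**The concern.** A test of effect modification needs a modifier that treatment allocation cannot influence. Here the cut-off for measuring the modifier is the treatment itself.

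Suppose a delayed-arm participant has a recurrent stroke or a symptomatic HT after randomisation and before the DOAC starts. The scan that diagnoses it is the last one before DOAC, so the event enters the model as the outcome and also as a larger baseline infarct or as baseline HT. In the early arm the same event usually falls after DOAC start, so its scan is ineligible and the earlier scan is used. Large infarcts and HT then look harmful in the delayed arm only. The interaction shifts towards early DOAC being better in those patients, whereas the plan expects early DOAC to be less favourable there. A true harm could be hidden or reversed.

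Infarct extent and HT also change over days, so even without an outcome event they may be read at different stages in the two arms. The Discussion says primary-exposure results are meant to influence practice, and both primary exposures are involved.

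**Working it through.** **The plan's own counts.** From Sample size estimates: target 3,478, 5% loss, 4.3% outcome rate.
- Infarct and HT: 3,478 × 0.57 × 0.95 = 1,883; × 0.043 = 81 events. Agrees.
- MRI markers: 3,478 × 0.24 × 0.95 = 793, against 790 stated; 34 events. Agrees to rounding.
- CT small vessel disease: 3,478 × 0.95 = 3,304; × 0.043 = 142 events. Agrees.

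All availability shares are pooled. None is given by arm, or by time relative to randomisation.

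**Scan window.** From the day limits in Study setting, the ratio of closing times (delayed to early) is 7/4 = 1.75 to 14/4 = 3.5.

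**Infarct volume.** Simulation with no treatment effect and no interaction: 3,648 participants, 4.3% events, logistic model with treatment × standardised log volume, no site effect. Assumptions: a delayed-arm event before DOAC start adds a lesion drawn from the same volume distribution, and the early-arm window is negligible. The ranges cover different assumptions about who has a usable scan. The true ratio of odds ratios (early/delayed, per SD) is 1 and the nominal error is 5%.

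| Assumed share of delayed-arm events before DOAC start | False ratio of ORs per SD | Type I error |
|---|---|---|
| 5-10% | 0.89-0.99 | 5-9% |
| 20% | 0.82-0.86 | 10-18% |
| 33% | 0.72-0.78 | 20-39% |

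If only half of these events change the measured volume, type I error at 20% and 33% falls to about 8% and 11%. For scale, a constant hazard over 5 to 10 of 90 days puts 5/90 = 6% to 10/90 = 11% of events before DOAC start. Front-loaded recurrence would raise that. The plan gives no figure.

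**HT.** Assume 1:1 allocation (1,883/2 ≈ 941 per arm) and 8% HT prevalence.
- Events per arm: 941 × 0.043 = 40.5, of which 3.24 with HT and 37.2 without.
- Non-events: 900.5, of which 72.0 with HT and 828.5 without.
- Recode 2 delayed-arm bleeds as baseline HT: OR = (5.24 × 828.5)/(72.0 × 35.2) ≈ 1.71, so the false early/delayed ratio is 1/1.71 ≈ 0.58.
- Recode 3: OR = (6.24 × 828.5)/(72.0 × 34.2) ≈ 2.10; ratio ≈ 0.48.

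The estimate moves a long way, but with so few HT cases the test rejects in only about 4% (2 bleeds) and 8% (3 bleeds) of runs. With about 4 recoded events and prevalence between 3% and 10%, the ratio is 0.21 to 0.47 and rejection about 13-14%.

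**MRI inclusion.** If a quarter of the pooled 24% with MRI were scanned at a constant rate up to DOAC start (assumed), inclusion would be 22% early against 26% delayed (delayed start on day 7), or 21% against 27% (day 14). If none were, inclusion would be equal.

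**Do other sections remove the problem?** The sensitivity analyses under Statistical analysis (dropping CT before 24 hours, CT only, MRI only) leave the window unequal. Dropping early CT leans more on later scans. Missing exposures are not imputed, so any selection by arm stays.

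**The case against.** The Discussion gives two reasons for the rule: it mirrors the imaging a clinician would have when choosing the timing, and it avoids drug effects on the scan. Both are sound aims, and a pre-randomisation scan meets both. Neither reason addresses the unequal windows.

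Several features limit the damage, and these points stand. MRI is preferred for infarct volume, so a later CT does not replace an existing MRI. HT is defined for the qualifying infarct, so a bleed elsewhere need not be coded. Systemic embolism adds no brain lesion. Where the last eligible scan precedes randomisation, there is no problem for that participant.

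A reader might infer more than the documents support:
- *That every interaction test is biased.* All participants had a CT, and leukoaraiosis, lacunes and the CT score are chronic features. That set, the largest, should hardly differ by arm.
- *That exposure and inclusion do differ by arm.* The rule allows it; pooled figures cannot show it.
- *That outcome events bring otherwise unscanned people into the infarct analysis.* This needs a lower time limit on CT. Patient population sets none, the Discussion only considers 6 hours, and the 12-hour limit appears only in the sample size estimate. An apparent early-versus-delayed main effect also depends on this route.
- *That scan raters are unblinded.* The SAP does not say who selects scans or sees the DOAC date.

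The Discussion says Heidelberg grades 2 and 3 are excluded at entry, yet Imaging variables of interest keeps PH2 and remote haemorrhage as categories. In correctly enrolled patients these could appear only on later scans. This fits the concern, but it may simply be the full scale restated.

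**Conclusion.** The rule is wrong as written for infarct volume, infarct size and HT. It lets a variable that is treated as baseline be measured after randomisation, over a period set by allocation, and lets an outcome event define it. MRI marker analyses may be affected through who gets an MRI. CT small vessel disease analyses are barely affected.

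The direction of the outcome-recoding bias is clear: early DOAC looks better with large infarcts or HT, against the plan's hypothesis. Its size is not known. For infarct volume it runs from negligible inflation of the 5% error, if few delayed-arm events precede DOAC start, to as much as 39% if a third do and each one changes the measured volume. For HT, two or three recoded bleeds roughly halve the ratio of odds ratios, although the test seldom rejects. These figures rest on assumed event shares, HT prevalence and 1:1 allocation. The defect in the rule does not depend on them.

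**What to change.** For the primary analysis, define infarct volume, infarct size, HT and the MRI markers on the last eligible scan acquired before randomisation, with the same rule in both arms. Change the wording to match in Patient population, Imaging data quality assurance, Imaging variables of interest and the Discussion.

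State that no analysis uses a scan made at or after an outcome event. That exclusion alone would remove the main route, but it would still leave infarct and HT read at different stages in the two arms, so it does not replace the pre-randomisation rule.

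Keep the last-scan-before-DOAC rule as a labelled sensitivity analysis. Report scan timing and inclusion by arm, and recount the numbers under Sample size estimates.

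The cost is SAP wording, a new scan selection from images already collected, and a smaller sample. The plan does not give the share of scans made before randomisation, so the loss cannot be computed. As an illustration, if 60% to 100% of the 1,883 qualify, the infarct and HT set is 1,883 × 0.6 = 1,130 (49 events at 4.3%) to 1,883 (81 events).

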**Imaging variables of interest**

Our primary exposures of interest are:

- Infarct volume, measured manually through computer-assisted planimetry. Infarct volume will be measured on diffusion-weighted MRI sequences if available. If not, the last CT scan acquired prior to DOAC administration will be used.
- Presence of haemorrhagic transformation of the qualifying infarct classified by Heidelberg criteria as petechial (1a/HI1 or 1b/HI2), parenchymal (1c/PH1 or 2/PH2), or remote (3) (22).

Our secondary exposures of interest are:

- A semiquantitative classification of infarct size used previously in observational studies and in the ELAN trial (8,9,16), estimated using diffusion-weighted MRI if available, or the last eligible CT scan if not. Infarct size is classified as below:
- Minor: lesion <1.5cm maximum diameter in anterior or posterior circulation, or multiple tiny spots (“embolic shower”)
- Moderate: lesion in cortical superficial branch of anterior, middle or posterior cerebral arteries; in deep branch of middle cerebral artery; in internal borderzone territories; or two minor lesions
- Major: lesion involving complete territory of anterior, middle or posterior cerebral artery; lesion ≥ 1.5cm maximum diameter in brainstem or cerebellum; or two moderate lesions
- CT markers of cerebral small vessel disease:
- Leukoaraiosis measured through total simplified Fazekas scale (17)
- Presence of one or more lacunes according to STRIVE definition (14)
- Overall CT Small Vessel Disease score, comprising leukoaraiosis, lacunes, and atrophy (18)
- MRI markers of cerebral small vessel disease:
- Number of cerebral microbleeds on MRI, categorised as 0, 1, 2-4, and 5 or more.
- Presence of multiple cerebral microbleeds in strictly lobar distribution (suggestive of cerebral amyloid angiopathy)
- Presence of cortical superficial siderosis (focal or disseminated)
- White matter hyperintensity burden measured through total Fazekas score (19)
- Presence of one or more lacunes according to STRIVE definition
- Burden of MR-visible perivascular spaces in basal ganglia region, rated using an established five-level ordinal scale (20)
- Overall MRI Total Small Vessel Disease score, comprising leukoaraiosis, white matter hyperintensities, basal ganglia perivascular spaces and cerebral microbleeds (21)

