**Sample size estimates**

The target sample size for OPTIMAS is 3,478 participants. In an interim analysis of the first 2,965 participants, all participants had a CT, 33% had a CT after 12 hours, 24% had an MRI before DOAC commencement, and 57% had either a CT acquired between 12 hours and DOAC commencement or an MRI. Interim data suggests a primary outcome rate of 4.3% (7). Allowing a conservative 5% margin for missing or poor-quality imaging, we estimate a sample size of 1,883 participants (81 events) for analyses of infarct volume, infarct size and haemorrhagic transformation, 790 participants (34 events) for analyses of MRI markers of cerebral small vessel disease, and 3,304 participants (142 events) for analyses of CT markers of cerebral small vessel disease. Owing to the fixed sample size, formal power calculations were not appropriate.

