**Statistical analysis**

For each imaging variable of interest, we will test for modification of the effect of treatment allocation (early or delayed DOAC initiation) by including the imaging variable as an interaction term with the independent variable representing treatment allocation (based on the intention-to-treat principle) in a mixed-effects logistic regression model with the occurrence of the primary study outcome as the dependent variable. If there is a significant difference in NIHSS between the main trial groups, we will consider adjusting for stroke severity (NIHSS) at randomisation. We will adjust for clustering by including sites as random intercept terms. An interaction with p-value <0.05 will be accepted as statistically significant. We will not adjust for multiple comparisons, but significant interactions for our secondary exposures of interest will be treated as hypothesis-generating (23). We will not impute missing exposures of interest but will include in each analysis all participants for whom the relevant exposure of interest is available.

Additional secondary analyses may include:

- A sensitivity analysis excluding participants with CT imaging acquired between before 24 hours of stroke onset
- Sensitivity analyses around infarct size and volume assessed using CT only or MRI only
- Analysis of exposures of interest with respect to individual components of the primary study outcome (e.g. ischaemic stroke, ICH)
- The feasibility and reliability of automated approaches to the measurement of infarct volume

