Haemorrhagic transformation is relatively common after cardioembolic stroke and often delays anticoagulation (30,31). Participants with severe parenchymal or remote haemorrhagic transformation (grade 2 or 3 by Heidelberg classification) are excluded from OPTIMAS on safety grounds. However, minor haemorrhagic transformation (Heidelberg grade 1) is not clearly associated with worse clinical outcome (32), and has not yet been shown to affect the risk-benefit balance of early anticoagulation. As haemorrhagic transformation is anticipated to be a rare baseline characteristic in the study sample, we will investigate this question by combining CT and MRI data - the Heidelberg classification has been proposed to apply to both (22). We will perform sensitivity analyses to address the possibility that the prevalence and significance of haemorrhagic transformation may vary according to imaging modality, given the very high sensitivity of blood-sensitive MRI sequences.

To our knowledge, whether neuroimaging markers of cerebral small vessel disease should influence the timing of anticoagulation initiation after ischaemic stroke is largely unstudied. It is clear that cerebral small vessel disease is the main cause of intracerebral haemorrhage overall, and likely also accounts for the majority of intracerebral haemorrhage in patients taking oral anticoagulants (27). Although haemorrhagic transformation generally occurs within infarcted brain tissue, it might be hypothesised that the risk of haemorrhagic transformation would be higher in the presence of pre-existing vascular fragility. Of the various CT and MRI markers of cerebral small vessel disease, we selected the burden of cerebral microbleeds on MRI as a primary exposure of interest as it is the most prognostically significant marker of long-term ICH risk in patients taking antithrombotics (28), and also influences the risk of ICH after intravenous thrombolysis (29).

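### The haemorrhagic transformation exposure lists grades excluded at entry and can be read after randomisation, and one unpenalised interaction model is set for markers too rare to support it

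*SAP*

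**What the plan says.** The SAP section Imaging variables of interest makes presence of HT of the qualifying infarct a primary exposure and grades it as "petechial (1a/HI1 or 1b/HI2), parenchymal (1c/PH1 or 2/PH2), or remote (3"). The Discussion states: "Participants with severe parenchymal or remote haemorrhagic transformation (grade 2 or 3 by Heidelberg classification) are excluded from OPTIMAS on safety grounds". It adds that "haemorrhagic transformation is anticipated to be a rare baseline characteristic in the study sample", and for that reason CT and MRI are combined.

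Patient population admits imaging acquired before DOAC administration, and Imaging data quality assurance prefers the last such scan where several of one modality are usable. Neither section refers to randomisation. Study setting gives DOAC start as within 4 days of onset in the early arm and 7 to 14 days in the delayed arm.

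Among the secondary exposures are "Number of cerebral microbleeds on MRI, categorised as 0, 1, 2-4, and 5 or more" and "Presence of cortical superficial siderosis (focal or disseminated"), the latter recorded as present or absent. Sample size estimates expects 1,883 participants (81 events) for HT and "790 participants (34 events) for analyses of MRI markers of cerebral small vessel disease".

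Statistical analysis tests every exposure by its interaction with allocation in a "mixed-effects logistic regression model with the occurrence of the primary study outcome as the dependent variable", with site as a random intercept and significance at p<0.05. It does not say whether HT enters as present/absent or by grade, whether ordered scales enter as categories or as a trend, which test gives the p-value, or what happens when a cell has no events.

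**The concern.** There are two problems.

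The first is the definition of a primary exposure. Two of the listed grades should not be present at entry. If they appear on the scan used, they reflect an ineligible participant, a central reading that differs from the site's, or a bleed that developed later. The plan treats all three as baseline exposure. Because the scan is anchored to DOAC start, which allocation itself determines, the delayed arm has more time in which HT can develop and be imaged. The interaction would then compare groups that are no longer formed by randomisation alone.

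The second is sparse data. When an arm has no events within a level of a marker, the maximum-likelihood interaction odds ratio is zero or infinite and its Wald p-value carries no information. A site random intercept does not cure this. Without a stated coding or fallback, both would be chosen after the data are seen.

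The stakes are highest for HT, because the Discussion says primary-exposure results are meant to influence practice. The Discussion also calls microbleed burden a primary exposure, although Imaging variables of interest lists it as secondary.

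**Working it through.** **Exposure definition.** Grades 2 and 3 are in the classification but are said to be excluded at entry. At entry, therefore, parenchymal should mean 1c only, and remote should hold nobody. The scan used may be any up to DOAC start: up to day 4 from onset in the early arm, up to day 14 in the delayed arm. Imaging is collected throughout enrolment, so a post-randomisation, pre-DOAC scan qualifies. The primary outcome includes symptomatic ICH with symptomatic HT, so a symptomatic bleed on that scan can enter both sides of the model.

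**Plan's own totals.** Inputs from Sample size estimates: 3,478 participants, imaging availability 57% (HT) and 24% (MRI), 5% loss, 4.3% event rate.
- HT set: 3,478 × 0.57 × 0.95 = 1,883; × 0.043 = 81 events. Reproduced.
- MRI set: 3,478 × 0.24 × 0.95 = 793 (stated 790); × 0.043 = 34 events. Reproduced within rounding.

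**Chance of an arm with no events.** Assumptions: 1:1 allocation, the overall event rate in every level, and prevalences shown as ranges because the plan gives none.
- Participants per arm in a level: m = N × prevalence / 2.
- Expected events per arm: m × 0.043.
- P0 = (1 − 0.043)^m; chance that at least one arm is empty = 1 − (1 − P0)².

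| Marker | N | Assumed prevalence | Events per arm | Chance of an empty arm |
|---|---|---|---|---|
| Siderosis | 790 | 0.5% | 0.08 | 99% |
| Siderosis | 790 | 2% | 0.34 | 91% |
| Siderosis | 790 | 4% | 0.68 | 75% |
| Microbleeds, 5 or more | 790 | 2% | 0.34 | 91% |
| Microbleeds, 5 or more | 790 | 8% | 1.36 | 44% |
| HT grade 1c alone | 1,883 | 1% | 0.40 | 89% |
| HT grade 1c alone | 1,883 | 2% | 0.81 | 68% |
| HT, binary | 1,883 | 3% | 1.21 | 49% |
| HT, binary | 1,883 | 5% | 2.02 | 24% |
| HT, binary | 1,883 | 10% | 4.05 | 3% |
| HT, binary | 1,883 | 15% | 6.07 | under 1% |

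Example, siderosis at 4%: m = 790 × 0.04 / 2 = 15.8; P0 = 0.957^15.8 = 0.499; 1 − 0.501² = 0.75. Simulation, which lets the number in the level vary, gives 76%.

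**Four-level microbleeds as categories.** Chance of at least one empty arm-by-level cell, by simulation, for assumed prevalences of 1, 2-4, and 5 or more:
- 8/5/2%: 98%
- 11/7/5%: 89%
- 15/12/8%: 65%

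Even with perfectly even spread, 34 events over 4 levels × 2 arms is 34 / 8 = 4.25 per cell.

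**Threshold.** A level expects fewer than one event per arm when its prevalence is below 2 / (N × 0.043): 2.5% in the HT set and 5.9% in the MRI set.

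**Power for binary HT at 10%.** The variance of the log ratio of odds ratios sums 1/events + 1/non-events over four cells: 2 × (1/4.05 + 1/90.1) + 2 × (1/36.4 + 1/810.9) = 0.574, so SE = 0.76. Power = Φ(ln R / 0.76 − 1.96): about 15% for R = 2 and 31% for R = 3.

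**The case against.** The strongest reply is that the primary HT exposure is worded as presence of HT, and the Introduction states the hypothesis for patients with HT as a group. On that binary reading the model is usually estimable, and the Heidelberg grades merely describe it. This stands. A reader might infer that one of the two primary tests will fail; the documents do not support that. Binary HT becomes fragile only near 3% prevalence.

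Nor do the documents support saying that cells are expected to hold no events. They give no prevalences, only that HT should be rare. The siderosis and microbleed figures are conditional on assumed ranges.

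A reader might also infer that any PH2 or remote bleed on the scan must be an outcome. That does not follow. Only symptomatic ICH counts, and central reading of a pre-randomisation scan could assign a grade that the site did not. Recording the full scale is not itself an error.

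The plan does not specify a Wald test. A likelihood-ratio test remains computable with an empty cell, and microbleeds entered as a trend would usually be estimable. A claim that most MRI tests fail is not shown, because fazekas score, lacunes, perivascular spaces and the total score were not quantified. The MRI markers listed are secondary and hypothesis-generating.

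Finally, the plan deliberately uses imaging before anticoagulation, to reflect how imaging might guide the timing decision and to avoid DOAC effects on the scan. That excludes drug effects but not the unequal time before DOAC start in the two arms.

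**Conclusion.** The point holds in a limited form. The inclusion of grades 2 and 3 conflicts with the stated exclusion and must be reconciled. The scan window allows a primary exposure to be measured after randomisation for unequal lengths of time; its size cannot be computed, because the plan does not say how many pre-DOAC scans follow randomisation.

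The sparse-data problem is likely for siderosis and for microbleeds if entered as four categories, and for HT only if it is entered by grade. These conclusions assume 1:1 allocation, a 4.3% rate in every level and the stated prevalence ranges. The siderosis result is not sensitive to the rate: doubling it at 2% prevalence still leaves a 74% chance of an empty arm. Binary HT is a problem of power more than of estimability.

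This should be changed before analysis, but it does not show that the primary HT test will break down.

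**What to change.** - Define the primary HT exposure as Heidelberg grade 1 (1a-1c) present versus absent on the last scan before randomisation. Keep the last pre-DOAC scan as a sensitivity analysis.
- Report subgrades descriptively. List any grade 2 or 3 finding separately, as an eligibility deviation or a post-randomisation bleed, and align the exposure list with the Discussion.
- Enter microbleed category and the other ordered scales as a 1-df trend by treatment, with the categorical version descriptive.
- Name in advance the rare markers (siderosis, multiple strictly lobar microbleeds) whose interaction will be tested by Firth-penalised likelihood ratio. For any other marker, use that test only if an arm-by-level cell has no events. A trigger of fewer than 5 events would be too wide: at 10% prevalence it would fire on binary HT itself, at about 4 events per arm.

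The cost is a few lines of SAP text and standard software. The downsides are that a trend assumes monotone modification, the penalised fit does not model site, and some participants will lack a pre-randomisation scan of the required type, in a number the plan does not give. The changes make the tests well defined but add no information, so power stays low.
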